#### 5.1.2.4 Other medical histories

- Known hypersensitivity to one of the trial drugs or to one of its excipients, as well as to one of the following compounds: chloroquine and other 4-amino quinolines, amodiaquine, mefloquine, glafenine, floctafenine, antrafenine, ARB.
- Presence of one of the following illnesses reported by the person: hepatic porphyria, known obstructive hepatobiliary disease, liver failure (score  $\geq$  Child-Pugh B), chronic kidney disease stage 4 or 5 (GFR  $<30$  mL/min/1.73 m^2) or dialysis, retinopathy, lactose hypersensitivity, anomalies in galactose metabolism, lactase deficiency, malabsorption syndrome, known glucose-6-phosphate-dehydrogenase deficiency, symptomatic gout/hyperuricemia.

### 5.2 Trial treatments

The trial treatments shall be as follows:

#### 5.2.1 Vitamins

- AZINC Forme et Vitalité®
- 2 tablets *QD* from Day 0 to Day 9
- To be kept below 25°C

#### 5.2.2 Hydroxychloroquine

- Brand name: Plaquenil®
- 200 mg per tablet
- 2 tablets *BID* on the day of inclusion (Day 0), then 2 tablets *QD* from Day 1 to Day 9
- To be kept below 25°C

#### 5.2.3 Imatinib

- Brand name: Imatinib TEVA®
- 400 mg per tablet
- 1 tablet *QD* from Day 0 to Day 9 (Day 0: at any time after inclusion; from Day 1 to Day 9: to be taken at 08:00 am)
- To be kept below 25°C

#### 5.2.4 Favipiravir

- Brand name: Avigan®
- 200 mg per tablet
- 12 tablets *BID* on Day 0, then 6 tablets *BID* from Day 1 to Day 9
- To be stored at below 25°C

#### 5.2.5 Telmisartan

- Brand name: Micardis®

- 20 mg per tablet
- 1 tablet per day from Day 0 to Day 9
- To be kept below 25°C

### 5.2.6 Concomitant drugs

Drugs whose taking is indicated as a criterion for non-inclusion (please see paragraph **Erreur ! Source du renvoi introuvable.**) shall be contra-indications of prescription over the 10 days following inclusion.

In all the arms, the usage rules for additional drugs that could be taken for symptomatic purposes, including paracetamol, shall be explained. A prescription for such treatments could be drawn up by the Doctor of the mobile study team, in close collaboration with the attending physician. For participants without any possibility of having third parties collect these drugs from the chemist's, the mobile study team, in collaboration with the attending physician, shall make the appropriate provisions.

### 5.2.7 Experimental drugs circuit

The drugs shall be ordered, received and kept at the CHU de Bordeaux - Pellegrin Hospital pharmacy. They shall be re-labelled on their original commercial packaging with a label in compliance with ICH recommendations on clinical research.

Drugs provided in the context of the trial shall be prescribed by the researcher by means of a prescription and a copy of that prescription shall be kept at the pharmacy [SDPM].

All drug containers, full, empty or opened, shall be returned to the pharmacy by the medical team, then kept until the monitoring visit of the pharmacy by the Clinical Research Assistant (CRA) for the trial. No destruction can be carried out without the written authorisation of the sponsor.

One or more monitoring visit(s) of pharmacies shall be carried out by the CRA for the trial.

During this/these visits, the CRA is to verify:

- the conditions under which the drugs are stored (temperature, humidity).
- the methods of dispensing experimental drugs.
- reconciliation between those experimental drugs received, in stock, dispensed and the units of returned experimental drugs.
- documentation for the trial.

## 5.3 Progress of the trial

### 5.3.1 Overview

The trial team is to implement mobile medical teams. These teams are to collaborate closely with the attending physicians, the coordinating physician of the nursing homes, medical call centres, diagnostic centres, and emergency services operating in Bordeaux and its surroundings, SOS Doctors and Centre 15.

Participants are to be recruited and monitored according to the following schedule:

**Table 1: Schedule of visits**

|                                    | Inclusion
Day 0 | Day
1
(1) | Day
3
(1) | Day
5
(1) | Day
7 | Day
9
(1) | Day
12
(1) | Day
14
(1) | End
(1)
(2) |
|------------------------------------|----------------------------|--------------------------|--------------------------|--------------------------|------------------|--------------------------|---------------------------|---------------------------|----------------------------|
| Clinical examination        |                            |                          |                          |                          |                  |                          |                           |                           |                            |
| Main study                  |                            |                          |                          |                          |                  |                          |                           |                           |                            |
| Information                        |                            |                          |                          |                          |                  |                          |                           |                           |                            |
| Physical examination               | X                          |                          |                          |                          | X                |                          |                           | X                         | X                          |
| Electrocardiogram (3)              | X                          |                          |                          |                          | (4)              |                          |                           |                           |                            |
| SpO2 measurement                   | X                          |                          |                          |                          | X                |                          |                           |                           | X                          |
| Eligibility criteria               | X                          |                          |                          |                          |                  |                          |                           |                           |                            |
| Signature of consent               | X                          |                          |                          |                          |                  |                          |                           |                           |                            |
| Randomisation                      | X                          |                          |                          |                          |                  |                          |                           |                           |                            |
| Distribution of the drugs          | X                          |                          |                          |                          |                  |                          |                           |                           |                            |
| Clinical appointment               |                            | X                        | X                        | X                        |                  | X                        | X                         |                           |                            |
| Receipt of AR/SAR                  | X                          | X                        | X                        | X                        | X                | X                        | X                         | X                         | X                          |
| Acceptability sub-study (6) |                            |                          |                          |                          |                  |                          |                           |                           |                            |
| Appointment                        |                            |                          | X                        | X                        |                  | X                        |                           |                           |                            |

| Swab                           |    |   |   |   |    |   |   |    |  |
|--------------------------------|----|---|---|---|----|---|---|----|--|
| Main study              |    |   |   |   |    |   |   |    |  |
| Nasopharyngeal swab            |    |   |   |   | X  |   |   | X  |  |
| Blood sample                   | X  |   |   |   | X  |   |   | X  |  |
| Volume of blood sampled (ml)   | 10 |   |   |   | 10 |   |   | 10 |  |
| Immunological sub-study |    |   |   |   |    |   |   |    |  |
| Blood sample                   | X  |   |   |   | X  |   |   | X  |  |
| Auto-test (drop of blood)      | X  | X | X | X | X  | X | X |    |  |
| Volume of blood sampled (ml)   | 3  |   |   |   | 3  |   |   | 3  |  |

(1) Telephone call.

(2) On Day 28, for people never hospitalised, 7 days after date of discharge from hospital, if not.

(3) The table indicates the ECGs carried out systematically at home by the mobile team. Other ECGs can be carried out in the interim, upon the referring cardiologists' indication, by means of a self-testing remote device

(4) Only those participants taking drugs which have any potential effect on the QT interval or those presenting a QTc between 460 and 500ms on the first electrocardiogram.

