| NUMBER OF CENTERS                                                   | The study takes place on an outpatient basis with follow-up at home and by telephone.                                                                                                                                                                                                                                                                                                                                                                                                                                                                                                                           |
| DURATION                                                            | 
Inclusion period: 3 months
 
Participation duration: 28 days.
                                                                                                                                                                                                                                                                                                                                                                                                                                                                                                                                       |
| ANALYSIS                                                            | 
This is a Phase III trial. Sequential analyses will be performed for the primary endpoint at D14, with the following objectives:
 
 
- Intermediate analysis #1 (30 included patients per arm): futility
 
- Intermediate analysis n°2 (60 patients included per arm): futility
 
- Intermediate analysis n°3 (102 patients included per arm): futility and early efficacy
 
- Final analysis: efficacy
 
                                                                                                                               |

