### 4.3 Judgement criteria

#### 4.3.1 Main criterion

The main criterion shall be the proportion of participants with an occurrence of hospitalisation and/or death between Day 0 and Day 14 in each arm.

All hospitalisations shall be taken into account, whatever may be their reason. Hospitalisation criteria, however, shall be standardised and specified in a specific procedure [SDPM].

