#### 4.3.2 Secondary criteria

- Hospitalisation proportion and its causes between Day 0 and Day 28 within each group
- Proportion of deaths and their causes between Day 0 and Day 28 within each group
- Intensive care hospitalisation proportion and its causes between Day 0 and Day 28 within each group

---

 Currently, the following criteria are being proposed: SpO2 < 92% in ambient air or 4% reduction in SpO2 since inclusion; respiratory rate > 30 min; heart rate > 130/min; systolic blood pressure < 90 mmHg or diastolic < 60 mmHg; other parameters indicating hospitalisation, in the judgement of the attending physician (for example, unexplained fall, severe digestive problems, reoccurrence or persistent fever > 38.5°C etc.)

- Proportion of patients with a reversion of SARS-CoV2 RT-PCR on a nasopharyngeal swab on Day 7 and Day 14, in each group
- Proportion of patients with a loss of autonomy evaluated by ADLs and IADLs on Day 14 and Day 28
- Changes in CBC, inflammatory markers (please see paragraph **Erreur ! Source du renvoi introuvable.**) and immunological markers (please see paragraph **Erreur ! Source du renvoi introuvable.**) from Day 0 to Day 7 and Day 14 in each group
- Number and proportion of adverse events of grades 1, 2, 3, 4 between Day 0 and Day 14 in each group
- Number and proportion of adverse reactions of grades 1, 2, 3, 4 between Day 0 and Day 14 in each group
- Plasma trough concentration of experimental drugs in the study on Day 7
- Acceptability of the treatment

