#### 5.3.8 Visit at the end of the trial (Day 28 or later)

- This is to take place:
  - On Day 28 for patients never hospitalised

- 7 days after the date of discharge from hospital if not
- The visit at the end of the trial shall be carried out by means of the web software allowing video contact, if the participant has an internet connection available and is capable of using it in the appropriate manner; or by telephone if the opposite applies.
- The visit at the end of the trial shall be devoted to:
  - Clinical condition (including the recording of undesired effects)
  - Taking of drugs
  - Mental state
  - Discussion on the progress of the patients' convalescence
  - Advice on the remaining days of convalescence
  - Information on receipt of the trial results

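### The last contact after a hospital stay has no Day 28 minimum, so D28 vital status, ICU readmission and autonomy are not scheduled for anyone discharged before D21

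*Protocol*

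**What the plan says.** The protocol states the timing of the last contact in two operative places, and they agree with each other. Table 1, note (2): "On Day 28, for people never hospitalised, 7 days after date of discharge from hospital, if not". Section 5.3.8, for those who were hospitalised: "7 days after the date of discharge from hospital if not". Neither sets a minimum of Day 28, and neither carries the tag that defers details to the procedures manual.

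Two other places imply follow-up to Day 28 for all. The heading of section 5.3.8 dates the visit at Day 28 or later, and the Summary states "Participation duration: 28 days".

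Several secondary criteria in section 4.3.2 need information up to or at that day: "Proportion of deaths and their causes between Day 0 and Day 28 within each group", "Hospitalisation proportion and its causes between Day 0 and Day 28 within each group", the matching intensive care proportion, and "Proportion of patients with a loss of autonomy evaluated by ADLs and IADLs on Day 14 and Day 28". Section 6.3.6 analyses secondary endpoints by intention to treat on available data.

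The main criterion in section 4.3.1 is earlier: "the proportion of participants with an occurrence of hospitalisation and/or death between Day 0 and Day 14 in each arm".

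**The concern.** The length of scheduled follow-up depends on whether the participant was hospitalised, which is a component of the outcome that the drugs are meant to change. A participant who is never admitted is contacted on D28. One who is admitted and discharged early has a last planned contact before D28.

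What happens after that contact is found only by chance, and the affected group differs in size between arms whenever a drug works. The available-data rule does not cure this. If early leavers are left out of D28 mortality, the control denominator of survivors shrinks more and control mortality looks too high. If they are counted as alive, more late control deaths could be hidden. The two errors run in opposite directions, and information never collected cannot be recovered at analysis.

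Preventing death by D28 is the first secondary objective in section 3.2, and preventing ICU admission and loss of autonomy are also listed there.

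**Working it through.** **1. When the rule falls short.** Last contact = discharge day + 7. This is before D28 exactly when discharge is before D21. Discharge on D21 gives 21 + 7 = 28; discharge on D20 gives 27.

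**2. Which D28 information is affected in those discharged before D21.**

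| Item | Status |
|---|---|
| Hospitalisation D0–D28 | Already an event; not lost |
| Hospitalisation or death at D28 (sensitivity analysis, 6.3.4) | Already an event; not lost |
| ICU care during the index stay | Before discharge; observable |
| ICU care on a readmission after the last contact | No scheduled contact |
| Death up to discharge + 7 days | Observable |
| Death from then to D28 | No scheduled contact |
| ADL/IADL at D28 | No scheduled contact on that day |

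**3. The design rates.** Section 6.2.1 assumes 25% events in control, a halving to 12.5%, 80% power and one-sided tests, and arrives at 169 per arm. It gives no numerical final efficacy alpha, so one-sided 0.025 is assumed here to check that these rates are the ones behind 169:

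- Without continuity correction: n = [1.96·√(2·0.1875·0.8125) + 0.8416·√(0.25·0.75 + 0.125·0.875)]² / 0.125² = 152.
- With continuity correction: (n/4)·[1 + √(1 + 4/(n·0.125))]² = 168, against 169 stated.
- At one-sided 0.05 the results are 120 and 136.

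The rates are therefore a fair basis for sizing the group. The sample size itself is not in question.

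**4. Participants with the primary event.** Control: 0.25 × 169 = 42.25. Effective arm: 0.125 × 169 = 21.125.

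**5. How many of them have a last contact before D28.** The protocol gives no length of stay. Assume the same stay L in both arms, admission days equally likely over D0 to D14 (15 days), and all hospitalised and discharged alive. The share affected is the fraction of admission days d with d + L + 7 < 28.

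| Assumed stay | Range of last contact | Share before D28 | Control, of 169 | Effective arm, of 169 | Median days short of D28, in those affected |
|---|---|---|---|---|---|
| 5 days | D12–D26 | 15/15 = 100% | 42 | 21 | 9 |
| 10 days | D17–D31 | 11/15 = 73% | 31 | 15 | 6 |
| 14 days | D21–D35 | 7/15 = 47% | 20 | 10 | 4 |
| 20 days | D27–D41 | 1/15 = 7% | 3 | 1 | 1 |
| 25 days | D32–D46 | 0 | 0 | 0 | – |

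With equal stays the ratio is 42.25/21.125 = 2 at every length that affects anyone. If those affected were omitted from D28 mortality with a 10-day stay, the denominators would be 169 − 31 = 138 and 169 − 15 = 154.

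**6. Autonomy.** The contents listed for inclusion (5.3.3), remote visits (5.3.5), face-to-face visits (5.3.6), the end visit (5.3.8) and Table 1 were compared with the criterion in 4.3.2. None names ADL or IADL, at baseline or later, for any participant.

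**The case against.** The strongest reply is that this is a slip of wording. The 5.3.8 heading and the 28-day participation show that D28 was meant for everyone, and section 6.3.3 plans to describe endpoints at D28. That is probably the intention, but the bullet and the table note are what a mobile team will follow, and both say otherwise.

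A second reply is that safety surveillance fills the gap. Hospitalisation is a serious adverse event, section 5.4.3.2 requires such events to be followed to resolution or stabilisation, and section 8.2 gives the DSMB daily counts of hospitalised and deceased participants. This narrows the gap without closing it. Under 5.4.3.1, adverse events are reported only to the end of participation. After the research has ended, 5.4.3.2 asks for a serious event only if the investigator learns of it and suspects a causal link. None of these provisions schedules a status check at D28.

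A third reply is that visit lists are summaries and ADL/IADL may stand in the procedures manual. That is possible, but the lists do not refer to it for this item.

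A reader might also infer that everyone with the primary event leaves before D28 and that all D28 endpoints are lost in them. The documents do not support that. Discharge on D21 or later leads to a contact on D28 or after, so the longest stays are followed in full. Hospitalisation to D28 and the D28 composite are already counted as events, and index-stay ICU care and deaths up to discharge + 7 days are observed.

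**Conclusion.** The protocol contradicts itself on the timing of the last contact. As the operative rule is written, participants discharged before D21 have no scheduled contact on D28. In them, death or ICU readmission after discharge + 7 days and ADL/IADL at D28 are not ascertained by schedule, and the loss depends on a component of the outcome and so on arm.

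The size depends on length of stay, which the protocol does not give. From a 5-day to a 20-day stay the number affected runs from about 42 against 21 to about 3 against 1 per 169. It rests on the design event rates, equal stays in both arms, uniform admission days and no deaths among those with the event. The figures count early last contacts; missed deaths or ICU stays would be a subset of unknown size. Reading 42 against 21 as the expected loss would be wrong, because it is the upper end.

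Neither the D14 primary endpoint, the interim decisions nor the sample size is touched: anyone under the short rule by D14 already has the primary event. Only secondary endpoints are affected, so this should be fixed but does not threaten the main conclusion. The missing ADL/IADL assessments are a related gap that concerns all participants.

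**What to change.** Reconcile Table 1 note (2) and the body of 5.3.8 with the heading and the Summary, for example: Day 28 for everyone; for those hospitalised, Day 28 or 7 days after discharge, whichever is later. State that vital status, readmission, ICU stay and adverse events are recorded to D28 for all participants. Add ADL/IADL at D0, D14 and D28 to Table 1 and to the matching visit contents, so that loss of autonomy has a baseline and a scheduled measurement.

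The cost is a small amendment, one later telephone call for each participant discharged before D21, and a short questionnaire at existing contacts. Treatment, sample size and the primary analysis do not change.

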### 5.3.3 Inclusion (Day 0)

If the test is positive, the process leading to inclusion and inclusion itself shall take place: At the outpatient COVID-19 screening unit or in A&E, if the person is still there at the time of the results becoming available; by visit by the mobile medical team to the home or Nursing Home, if the person has returned home or lives in the Nursing Home and agrees to being seen by the team.

The test result shall be explained to the person, who shall be invited to participate in the trial. If the person is interested, the conditions for inclusion shall be checked with him/her (including the review of all treatments in progress, a systematic ECG and recourse to cardiological opinion or the on-call cardiologist for the trial for persons on each occasion that it is appropriate).

If the criteria for inclusion have been met and there is no criterion for non-inclusion, all the questions on the trial shall be answered and they shall be asked whether they agree to participate. If they agree, they are to sign with informed consent and are to be included.

After signing the consent, the inclusion visit shall include:

- Physical examination
- Pulse oxygen saturation (SpO2)
- Blood sample
- Randomisation

- Drug delivery
- Advice

Participants are to receive a document explaining what they must do in the event of symptoms suggesting a worsening of the disease or any side-effect of the drug. During the inclusion visit, particular attention is to be drawn to the living conditions of solitary people, their environment in matters of food and access to drugs other than those delivered in the context of the trial and their ability to gain access to the telephone. In the event of any problem with one of these points, suitable solutions are to be found [SDPM].

People with a QTc between 460ms and 500ms upon inclusion, or any other risk factor requiring cardiological opinion before a decision on inclusion, shall be referred to a 6 lead ECG (Kardia Mobile 6L from AliveCor; CE N°72133041) daily monitoring and shall receive the necessary advice on its functioning during the inclusion visit. This user-friendly device allows transmission of the ECG results and remote reading by the research cardiologist for the trial.

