#### 5.4.2 Description of expected adverse events

Expected adverse events for the trial's drugs are those specified in the Summary of Product Characteristics (SPC) for Plaquenil®, Imatinib TEVA®, Avigan® and Micardis®.

The Summary of Product Characteristics (available online on the trial eTMF) provides the complete list and the level of risk for each drug. The risks of adverse reactions for the 4 experimental drugs for short treatments of 10 days are slim. Adverse reactions, whether the most frequent (even if they are benign) or the most serious (even if they are rare) are as follows:

- Hydroxychloroquine: abdominal pain, diarrhoea, nausea, vomiting, lengthening of the QT interval and *torsades de pointes* or ventricular tachycardia, hypersensitivity, medullar aplasia, pruritus, rash, headache and hypoglycaemia.
- Telmisartan: rash, orthostatic hypotension, cardiac decompensation, hypersensitivity and elevation of transaminases.
- Imatinib: cardiac decompensation, elevation of transaminases, neutropenia, thrombocytopenia, anaemia, pancytopenia, headache, dyspnoea, cough, abdominal pain, vomiting, nausea, diarrhoea, cramps and water retention.
- Favipiravir: elevation of transaminases, diarrhoea, nausea, vomiting, headache, hyperuricemia and hypertriglyceridemia.

Any adverse event, neither appearing in the list of expected events, nor in the latest version of the benchmark document, is deemed to be unexpected.

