#### 5.4.3 Conduct to be maintained by the researcher in the case of adverse event or new finding

##### 5.4.3.1 Reporting of adverse events (AE)

The researcher is responsible for reporting adverse events occurring between the date of signature of consent and the end of the participant's participation, apart from those detected before the first application of the trial's treatment. If the clinical or biological adverse event is present at the time of signature of consent, only its deterioration needs to be recorded.

In the context of this protocol, all adverse events must be reported.

The researcher is to record adverse events (clinical and biological) in the observations log. Such adverse events are researched upon every visit over the course of the study by the posing of questions and during the participant's clinical examination.

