### 6.3.1 General information on the statistical techniques used

Qualitative outcomes will be described in tables and graphs as follows: frequency, proportion, standard deviation of the proportion, two-sided 95% confidence interval. Comparisons between arms will use a Chi test or an exact Fisher's test (depending on the outcome distribution) if no adjustment is required or logistic or binomial regression otherwise.

Normality of quantitative outcomes will be checked graphically.

Normally distributed quantitative outcomes will be described in tables and graphs as follows: frequency, mean, standard deviation of the mean, two-sided 95% confidence interval. Comparisons between arms will use a Student's t test if no adjustment is required or a linear model otherwise.

Quantitative non-parametric outcomes will be described in tables and graphs as follows: frequency, median, range and interquartile range. Comparisons between arms will use a Wilcoxon or a Kruskal-Wallis test (depending on the number of strata) if no adjustment is required or a stratified analysis otherwise.

Time-to-event outcomes will be described in tables and graphs as follows: number, probability of event and two-sided 95% confidence interval estimated by the Kaplan-Meier method. Comparisons between arms will use a logrank test if no adjustment is required or a proportional risk (Cox) model otherwise.

Model assumptions will be checked before final adjustment.

Descriptive analyses will be systematically presented globally, by country, stratum and arm.

Comparisons between arms will be systematically performed:

- Without adjustment
- With adjustment on randomisation stratification factors
- With adjustment on randomisation stratification factors and on baseline prognostic factors which distribution could be unbalanced between arms despite randomisation.

Moreover, these adjustments will possibly imply the use of appropriate models not cited here. Their relevance will be discussed depending on the factors nature and distribution.

Details on secondary and exploratory analyses on the primary endpoint and analyses on secondary and exploratory endpoints will be provided in the statistical analysis plan.

The identification of determinants of events will be performed using univariate and stepwise multivariate selection models, which details will be defined in the statistical analysis plan.

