### 6.3.7 Safety analysis

The analysis will be performed on participants having taken at least one dose of randomisation treatment on available data, from D0 to D14 and D28.

Adverse events will be described through SOC and PT levels of MedDRA classification (last version at time of database freezing).

The incidence of adverse events will be described in terms of nature, causality, severity, intensity.

The incidence of adverse events related to randomisation treatment discontinuation or dosage modification will be described and compared between arms.

Safety analysis will be performed in compliance with the recommendations of the Consort Statement on harm.

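### The systematic Day 7 ECG depends on the drug taken, so ECG-only adverse events may be found more often on hydroxychloroquine than in control without any drug effect

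*Protocol*

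**What the plan says.** Table 1 (section 5.3.1) marks a systematic ECG at Day 0 for everyone. Note (4) limits the one at Day 7: "Only those participants taking drugs which have any potential effect on the QT interval or those presenting a QTc between 460 and 500ms". Note (3) adds that "Other ECGs can be carried out in the interim", when a cardiologist asks for them, by remote device.

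A separate daily 6-lead ECG is chosen on baseline features in every arm. Section 5.3.3 gives it to "People with a QTc between 460ms and 500ms upon inclusion, or any other risk factor requiring cardiological opinion before a decision on inclusion". Section 5.1.2.2 describes the same group: QTc 460–500 ms, a significant ECG anomaly, or a relevant cardiovascular history, monitored over the first seven days of treatment.

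Note (4) names no arm. In section 5.4.2, "lengthening of the QT interval" appears for hydroxychloroquine and for none of the other three trial drugs.

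On adverse events, section 5.4.3.1 says "In the context of this protocol, all adverse events must be reported". Section 4.3.2 makes this a secondary criterion: "Number and proportion of adverse events of grades 1, 2, 3, 4 between Day 0 and Day 14 in each group". Section 6.3.7 describes adverse events in general and adds one explicit comparison: "The incidence of adverse events related to randomisation treatment discontinuation or dosage modification will be described and compared between arms". Section 6.3.1 has a general rule: "Comparisons between arms will be systematically performed".

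**The concern.** A test done after randomisation, and ordered because of the drug received, feeds an adverse event count that is set side by side by arm. Day 7 lies inside the Day 0–14 window. A person on hydroxychloroquine with no cardiac risk feature has a Day 7 ECG; the same person in control does not. A new asymptomatic ECG abnormality would be recorded in the first case and missed in the second.

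Tolerance is a stated secondary objective (section 3.2), and the trial is open-label. Section 1.4.1 lets an arm be halted for safety with DSMB approval and without a formal statistical criterion, so no significance threshold stands between an ascertainment artefact and the people reading the table. The arm affected is the one whose cardiac toxicity section 1.4.3 singles out for attention.

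**Working it through.** The protocol states no figure on this point, so there is none to reproduce. The check has two parts: who is examined, and how large the gap could be.

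**Who has an ECG after Day 0**

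| Participant | Hydroxychloroquine | Control |
|---|---|---|
| Baseline QTc 460–500 ms | Day 7 ECG and daily 6-lead | Day 7 ECG and daily 6-lead |
| Other baseline cardiac feature (5.1.2.2, 5.3.3) | Day 7 ECG and daily 6-lead | Daily 6-lead |
| None of these | Day 7 ECG | None scheduled, unless on a QT-active co-medication |

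The 6-lead rule is the same in both columns. The main gap is the last row. Because section 5.4.3.1 records a condition already present at consent only if it worsens, the affected events are new or worsened findings seen only on the ECG.

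**How large it could be with no drug effect**

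Input from the protocol: n = 169 per arm (section 6.2.1), used only for scale. Assumptions, none of them in the protocol:
- b, the rate of reportable ECG findings at Day 7, equal in both arms: 2%, 5%, 10%
- f, the share of controls who have an ECG: 10%, 20%, 30%
- k, the rate of findings in examined relative to unexamined controls: 1 or 3 (examined controls are chosen for risk, so k above 1 is plausible)

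Expected findings on hydroxychloroquine = n·b. Expected findings in control = n·b·fk/(fk + 1 − f). Example with b = 5%, f = 10%, k = 3: 169 × 0.05 = 8.5 on hydroxychloroquine; 169 × 0.05 × 0.3/(0.3 + 0.9) = 2.1 in control. The last column is the chance that a two-sided Fisher test at 0.05 shows a false excess, summed over the two binomial distributions.

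| b | f | k | Hydroxychloroquine | Control | Chance of false excess |
|---|---|---|---|---|---|
| 2% | 10% | 1 | 3.4 | 0.3 | 9% |
| 2% | 30% | 3 | 3.4 | 1.9 | 3% |
| 5% | 10% | 1 | 8.5 | 0.8 | 65% |
| 5% | 10% | 3 | 8.5 | 2.1 | 39% |
| 5% | 20% | 3 | 8.5 | 3.6 | 19% |
| 5% | 30% | 3 | 8.5 | 4.8 | 11% |
| 10% | 10% | 1 | 16.9 | 1.7 | 96% |
| 10% | 30% | 3 | 16.9 | 9.5 | 25% |

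Under one ECG rule for both arms the expected counts are equal: 3.4, 8.5 or 16.9 in each. The same test is then significant in about 1–3% of trials.

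**Dilution in total adverse events**

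Let a share a of participants have some other adverse event (assumed 40% or 60%), independent of the ECG, with f = 10% and k = 1. The proportion with any event is a + (1 − a)b on hydroxychloroquine and a + (1 − a)bf in control.
- a = 40%, b = 5%: 0.40 + 0.60 × 0.05 = 43.0% against 0.40 + 0.60 × 0.005 = 40.3%; significant in about 7% of trials
- a = 60%, b = 5%: 62.0% against 60.2%; about 5%
- With no imbalance, this test is significant in about 4%
- At b = 10%: 46.0% against 40.6% (about 15%), and 64.0% against 60.4% (about 8.5%)

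**The case against.** The best case for the plan is that targeted safety ECGs are legitimate, that people at cardiac risk are already monitored alike in every arm, and that 6.3.7 tabulates events by MedDRA class and term, so ECG findings would sit on their own rows where a DSMB with pharmacovigilance expertise could interpret them. The monitoring is indeed not at fault, and the baseline-selected 6-lead ECG does shrink the gap. Separate rows do not remove it, however: nothing tells the reader that those rows were ascertained unequally.

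Other limits also stand. Note (4) refers to participants taking drugs; that this means the hydroxychloroquine arm is inferred from section 5.4.2. If other trial drugs count as QT-active, their arms are affected too and control remains under-examined. Explicit comparison in 6.3.7 covers only events tied to discontinuation or dosage modification; comparison of the other counts rests on the general rule in 6.3.1.

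A reader might infer that the artefact also inflates treatment discontinuations on hydroxychloroquine, since section 5.3.4 allows an ECG anomaly to stop the trial drug. The documents do not support this. That rule concerns people given the ECG device, who are chosen on baseline features and so are balanced by randomisation. No section links the Day 7 ECG to a stop, and dosing ends at Day 9.

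**Conclusion.** The point holds for a limited class of events: new ECG-only findings in participants without baseline cardiac risk features. For these, detection depends on the arm, and hydroxychloroquine may show more than control with no drug effect. Over the assumed ranges the expected counts are 3.4–16.9 against about 0.3–9.5. The chance of a nominally significant false excess runs from 3–9% at a 2% finding rate to 25–96% at 10%. These figures rest on assumed rates and shares examined, and on reading note (4) through section 5.4.2.

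Three stronger readings go too far. That an excess will certainly appear in the data cannot be said, because the protocol gives no rate of findings and at 2% the gap is about 1.5 to 3 events per arm. That total adverse events are seriously distorted does not follow either: at a 5% finding rate that comparison is barely disturbed, although it moves more at 10%. And the primary endpoint, hospitalisation or death, is not directly affected. The matter still deserves correcting, because tolerance is a stated objective and the correction is cheap.

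**What to change.** Leave the ECG monitoring unchanged and alter only how its results are recorded and presented.

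- Add a source-of-detection field to the adverse event form (symptom or visit, blood test, Day 7 ECG, 6-lead device, other).
- State in 6.3.7 that findings detected only by the drug-dependent Day 7 ECG are tabulated separately by arm, shown to the DSMB and labelled as unequally ascertained.
- State that between-arm adverse event comparisons are given both with and without these findings, so that a true QT effect stays visible.
- Make the between-arm ECG comparison among all participants selected for monitoring on baseline criteria (QTc 460–500 ms or the other features in 5.1.2.2), including their 6-lead findings. For those selected on features other than QTc, use the 6-lead findings only, because their Day 7 ECG still depends on the drug.

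The cost is one form field, a few sentences in the protocol and analysis plan, and one extra table. The downside is that the fair ECG comparison rests on a subgroup: at an assumed 10% selected, about 17 participants per arm (169 × 0.10), so it will be imprecise.
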